## Abstract

The effect of frailty on short and long term results of interventional treatment of coronary heart disease is not well defined. The evaluation of frailty may be helpful in appointment of most suitable treatment option and timing of patient follow-up. The frailty syndrome in daily practice of interventional cardiology ward (FRAPICA) study objective is to evaluate prognostic capability of the Fried frailty scale and instrumental activities of daily living scale (IADL) in elderly patients with symptomatic coronary heart disease.

This is a single center, prospective, observational study. Patients aged ≥65 years are eligible. The objectives are to report Fried frailty scale and IADL scale dispersion before hospital discharge and to assess predictive impact of both scores. The endpoints are: success of interventional treatment, its complications (procedure related myocardial infarction, dye-induced renal function deterioration, loss of blood), 3-year mortality, either all-cause and cardiovascular, re-infarction, re-intervention, stroke, new-onset heart failure, any hospital readmission, and a combination of all above mentioned. Secondary analyses will focus on distinct clinical patient presentations, sub-classifications of frailty for modeling of long-term risk.

FRAPICA trial will improve understanding of the associations between frailty syndrome, cardiovascular system diseases, their invasive treatment, and short and long-term outcomes. It will allow for more individualized assessment of risk and will identify new goals for interventions. (ClinicalTrials.gov Identifier NCT03209414)

## Introduction

1

Frailty gains growing attention of clinical research community as society of developed countries and their cardiovascular patients are aging. Frailty syndrome is characterized by reduced physiological reserve and increased susceptibility to various stressors.^[1]^ Several diseases, either acute or chronic, or iatrogenic circumstances may act as stressors. Frail patients, after being exposed to such stressors, may react with incommensurate decompensation, and adverse outcomes. They are at higher risk of procedural complications, long-lasting recovery, functional deterioration, physical disablement, and increased risk of death.^[2]^ The syndrome is frequently associated with comorbidities.^[3]^ Symptomatic coronary heart disease, either stable or unstable, is the prevailing disease unit among elderly patients. Inversely, data on prevalence of phenotype frailty among patients aged ≥65, who underwent percutaneous coronary angioplasty were recently published.^[4]^ Gharacholou et al^[4]^ reported that approximately 20% of those patients is frail. Moreover, frail patients have greater comorbid burden and greater angiographic coronary artery disease intensity. However, commonly used risk stratification scales, like Syntax,^[5]^ Euro,^[6,7]^ or GRACE^[8]^ use patient's age as a major determinant of risk, but they do not incorporate the frailty traits into the risk assessment. Technical development has allowed more patients to become eligible for interventional treatment.^[9,10]^ As medical innovations are cost consuming, the individual benefits of such medical procedures are not well defined in particular patient populations. Thus, we need to operationalize more detailed patient selection.

The objectives of the study are to report Fried frailty scale and instrumental activities of daily living (IADL) scale dispersion before hospital discharge and to assess the predictive impact of both scores in a population of elderly patients with symptomatic coronary artery disease.

## Materials and methods

2

### Patient population

2.1

The FRAPICA trial is a single center, observational, prospective, study. One thousand patients aged ≥65 years with symptomatic coronary heart disease will be enrolled. Patients with all clinical presentations of coronary artery disease are eligible. Stable coronary heart disease is diagnosed on the base of exercise induced ischemia, resolving after rest. Acute coronary syndrome includes ST segment elevation myocardial infarction, non-ST segment elevation myocardial infarction and clinical presentation of unstable angina. The latter is characterized by myocardial ischemic pain at rest or at minimal physical activity in the absence of myocardial necrosis. Non-ST segment elevation myocardial infarction is diagnosed in patients with symptoms of ischemia, electrocardiographic abnormalities such as ST-segment depression, inversion of T wave, flattened T wave, pseudo-normalization of previously negative T waves, and presence of cardiomyocyte necrosis. ST-segment elevation myocardial infarction is diagnosed when acute precordial pain (>20 minutes), persistent ST-segment elevation, cardiomyocyte necrosis, and typical angiographic findings are present.^[11]^ Either femoral or radial approaches are acceptable—the choice of puncture site depends on patient's or operator's preference and basically on medical conditions. Only patients with type 1 myocardial infarction are considered eligible for the study. Method of revascularization is decided by the operator and ad hoc percutaneous coronary intervention is sometimes performed. Mostly, this is a case in a low-risk patients with single vessel disease, or in cases of ST-elevation myocardial infarction (STEMI) or non ST-elevation myocardial infarction (NSTEMI) patients with identifiable culprit artery. Nevertheless, all coronary angiographies are assessed and discussed by a heart team, selected records are re-consulted with a cardiac surgeon and a further revascularization schedule is planned. For the risk stratification we use Syntax score and logistic Euro score. After performed coronary angiography and confirmation of coronary heart disease with documented significant stenosis, patients are screened and written informed consent is obtained. Protocol of the study was approved by Internal Review Board of Medical University of Silesia. For the purpose of this study we record demographic, clinical, laboratory, angiographic data from patient's medical charts, assess the presence of frailty syndrome, measure arterial stiffness, body composition, pulmonary function, and draw fasting blood for further analyses. Study flowchart is shown in Fig. 1.

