### Frailty assessment with Fried frailty scale and IADL score

2.2

We use Fried frailty phenotype score^[12]^ and Lawton and Brody score (IADL).^[13]^ We recognize frailty if ≥3 out of 5 following criteria are met^[12]^:

Slowness—reduced gait speed at a distance of 5 m at usual pace. Patient must repeat 3 times and the results are averaged. If a patient walks for >6 seconds then the criterion is classified positive.Weakness is assessed with maximal handgrip strength test. It is carried out in the dominant arm. We use electronic hand dynamometer EH101 (VETEK AB, Sweden). Patient must repeat 3 times and the maximal value is recorded. Test is positive for frailty when strength is lower than 20 kg for women and 30 kg for men.Low physical activity is assessed by Minnesota Leisure Time Activity questionnaire. The result is positive when calorie expenditure per week is lower than 270 kcal/wk in women and <383 kcal/wk in men. We have prepared a Microsoft Excel-based template for rapid questioning and easy calculation of all activities and respective calorie expenditure. We are assessing the physical activity from the recent 12 years.Exhaustion—self reported by a patient. It is evaluated by the answer to 2 questions from the Center for Epidemiologic Studies Depression Scale Revised (CESD-R) scale. Patient has to answer following questions: “How often in the past week did you feel like everything you did was an effort? How often in the past week did you feel like you could not get going?” The possible answers are: often (≥3 days) or not often, when the feeling is present in 0 to 2 days. Positive answer is when the patient says “often.”The last criterion is weight loss weight exceeding 10 pounds (appr. 4.5 kg) unintentionally in the past year.

Patients in whom 1 or 2 criteria are present will be assigned as pre-frail.

The Lawton IADL score is incorporated into CSHA Clinical Frailty Scale for description of mild to severe degrees of frailty.^[14]^ Moreover, even a single deficit in IADL score increases mortality rate by 56% in a cohort of patients with heart failure.^[15]^ We will compare patients with no deficits (IADL score equal to 24 points) with patients with different degrees of impairment (IADL score no >23 points).

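### In patients who have ad hoc PCI, frailty may be measured after the procedure whose success and complications it is meant to predict

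*Protocol article*

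**What the plan says.** **Order of enrolment.** Section 2.1 (Patient population): "After performed coronary angiography and confirmation of coronary heart disease with documented significant stenosis, patients are screened and written informed consent is obtained". The same section then lists frailty assessment among the measurements made for the study, so it comes after consent.

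**Ad hoc procedures.** Section 2.1 also says: "Method of revascularization is decided by the operator and ad hoc percutaneous coronary intervention is sometimes performed". It describes these as mostly low-risk single-vessel cases, or STEMI and NSTEMI with an identifiable culprit artery. The share of patients is not given. Femoral and radial access are both allowed.

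**Timing and use of the scores.** The Abstract states: "The objectives are to report Fried frailty scale and IADL scale dispersion before hospital discharge and to assess predictive impact of both scores". The Introduction says the same. No text shown requires testing before revascularization. The endpoints in the Abstract begin with "success of interventional treatment, its complications (procedure related myocardial infarction, dye-induced renal function deterioration, loss of blood", and go on to the 3-year outcomes. Section 2.7 gives periprocedural infarction and contrast nephropathy 48-hour windows.

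**The test items.** Section 2.2 calls a patient frail at three or more of five criteria: a 5 m walk, handgrip, physical activity, exhaustion in the past week, and weight loss over the past year. Of grip it says: "It is carried out in the dominant arm".

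**The concern.** Ad hoc PCI, in the usual sense of the term, is done in the same session as the diagnostic angiogram. In those patients the procedure is over before consent and before the frailty test. Its angiographic result is then known, and a bleed, infarct or rise in creatinine may already have occurred.

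Two biases may follow for the procedural endpoints.

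- **Reverse causation.** A bleed or infarct may slow gait, weaken grip or bring on exhaustion. A patient who already meets one or two criteria needs only one or two more to be classed as frail. The complication then helps to produce the frailty label that is later said to predict it. Grip has a further route: the dominant arm may be the arm just punctured for radial access.
- **Selection.** Patients who die, or are too ill to consent or be tested, never enter. The worst procedural outcomes are therefore under-represented.

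At stake are the short-term results. An association found there might be read as pre-procedural risk information when part of it arose from the procedure.

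**Working it through.** The protocol gives no figure for this association, so there is nothing to reproduce. The check has two parts.

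**1. Order of exposure and outcome, by type of case**

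| Case | Frailty test relative to outcome |
|---|---|
| Ad hoc PCI, procedural endpoints | Test follows the procedure; outcome may precede the test |
| Staged PCI or surgery done after the test | Test precedes the outcome |
| Medically treated patients | No revascularization outcome |
| 3-year events after the test | Test precedes the outcome |

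Only the first row is affected.

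**2. How large could reverse causation be?**

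Inputs:
- True frailty f = 0.20, from the Introduction, which cites about 20% in a published PCI cohort aged 65 and over.
- Complication risk c = 0.10, an assumption, varied below.
- No true association between frailty and complications.
- s = share of otherwise non-frail patients whom a complication makes test frail. This is an assumption, varied from 5% to 30%.
- All complications in ad hoc cases occur before the test, an assumption that makes the bias as large as it can be for a given s.

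Formulas within ad hoc cases:
- P(tests frail | complication) = q = f + (1 − f)s; without a complication it is f.
- Risk in those testing frail = cq / [cq + (1 − c)f].
- Risk in those testing non-frail = c(1 − q) / [c(1 − q) + (1 − c)(1 − f)].

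For s = 0.10: q = 0.20 + 0.80 × 0.10 = 0.28. Risk if frail = 0.028 / (0.028 + 0.18) = 13.5%. Risk if non-frail = 0.072 / (0.072 + 0.72) = 9.1%. Ratio = 1.48.

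| s | q | Risk, frail | Risk, non-frail | Spurious risk ratio |
|---|---|---|---|---|
| 5% | 0.24 | 11.8% | 9.5% | 1.23 |
| 10% | 0.28 | 13.5% | 9.1% | 1.48 |
| 20% | 0.36 | 16.7% | 8.2% | 2.04 |
| 30% | 0.44 | 19.6% | 7.2% | 2.72 |

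The complication risk matters little: over the same four values of s, the ratio runs from 1.25 to 2.92 at c = 5% and from 1.22 to 2.54 at c = 15%.

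**Dilution over all treated patients.** Assume 30% are ad hoc and the other 70% are tested first, with 10% risk whatever their frailty.
- s = 10%: frail (0.3 × 0.028 + 0.7 × 0.02) / (0.3 × 0.208 + 0.7 × 0.20) = 0.0224 / 0.2024 = 11.1%. Non-frail (0.3 × 0.072 + 0.7 × 0.08) / (0.3 × 0.792 + 0.7 × 0.80) = 0.0776 / 0.7976 = 9.7%. Ratio 1.14.
- s = 20%: frail 0.0248 / 0.2048 = 12.1%. Non-frail 0.0752 / 0.7952 = 9.5%. Ratio 1.28.

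This arithmetic covers the Fried classification and reverse causation only. It does not include selection, and it makes no claim about how far IADL answers would shift.

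**The case against.** The strongest reply is that the problem is narrow and partly acknowledged. Several points stand.

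- **Scope.** Ad hoc PCI is done only sometimes. Where revascularization follows testing, the order is right.
- **Items.** Weight loss covers a year, and the activity recall as printed runs to years. Exhaustion needs at least three days in the past week. A patient who met no criteria beforehand would have to turn positive on gait, grip and exhaustion together. Contrast nephropathy is a creatinine change with no evident route to slow gait or weak grip. High conversion is therefore hard to reach.
- **Acknowledgement.** Section 3 concedes that angina can slow gait and that admission or exacerbation can move a pre-frail patient to frail. It does not connect this with the procedural endpoints and gives no remedy, so it mitigates but does not settle the point.
- **Documents not shown.** The flow chart, the full protocol or an analysis plan may say more on timing. The text itself, however, places screening and consent after angiography, and analysis cannot restore the order unless test times were recorded.

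A reader might infer more than the text supports:

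- **That frailty cannot predict these events at all.** Several items describe the state before admission. The defect is possible misclassification that depends on the outcome, not the absence of a prior trait.
- **That the results must be biased toward more complications in frail patients.** If frail patients with complications more often die or become untestable, selection pulls the other way. The net direction is not known.
- **That the distortion is very large.** With 50% conversion the ratio within ad hoc cases would be 25% / 5.3% = 4.7, and with 60% ad hoc the overall ratio would be 19.6% / 7.2% = 2.7. Nothing in the document supports either input.

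**Conclusion.** The point holds for procedural success and safety endpoints in patients treated before they are tested. There the stated sequence lets the exposure be measured after the outcome, so the short-term association may be created or inflated by reverse causation, and selection on being alive and testable may shift it in either direction. The long-term objective is not undermined, provided that only events after testing are counted.

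The size cannot be derived from the document, because it gives neither the ad hoc share nor a conversion rate. The ratios above show only that modest conversion is enough to produce a visible association within ad hoc cases, and that it shrinks considerably when ad hoc cases are a minority. The plan should be changed on this point, but it is not a fatal flaw.

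**What to change.** 1. Record the date and time of the frailty and IADL tests relative to each procedure.
2. For procedural success and safety, limit the predictive analysis to procedures performed after testing. Report ad hoc cases as cross-sectional association only.
3. Start the 36-month follow-up at the frailty test and count only later events.
4. Keep the dominant-arm grip test, so that the section 2.2 definition is unchanged. Record the access side and repeat the analysis without readings from a punctured arm.
5. State that the results apply to patients alive and testable before discharge.

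The cost is one time field, one access-side field and some analysis wording. The real downside is fewer patients, and so less precision, in the procedural-endpoint analysis.

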
**Figure 1 F1:**
[figure not shown]
FRAPICA flow chart. FRAPICA = frailty syndrome in daily practice of interventional cardiology ward.

### Frailty assessment with Fried frailty scale and IADL score

2.2

We use Fried frailty phenotype score^[12]^ and Lawton and Brody score (IADL).^[13]^ We recognize frailty if ≥3 out of 5 following criteria are met^[12]^:

Slowness—reduced gait speed at a distance of 5 m at usual pace. Patient must repeat 3 times and the results are averaged. If a patient walks for >6 seconds then the criterion is classified positive.Weakness is assessed with maximal handgrip strength test. It is carried out in the dominant arm. We use electronic hand dynamometer EH101 (VETEK AB, Sweden). Patient must repeat 3 times and the maximal value is recorded. Test is positive for frailty when strength is lower than 20 kg for women and 30 kg for men.Low physical activity is assessed by Minnesota Leisure Time Activity questionnaire. The result is positive when calorie expenditure per week is lower than 270 kcal/wk in women and <383 kcal/wk in men. We have prepared a Microsoft Excel-based template for rapid questioning and easy calculation of all activities and respective calorie expenditure. We are assessing the physical activity from the recent 12 years.Exhaustion—self reported by a patient. It is evaluated by the answer to 2 questions from the Center for Epidemiologic Studies Depression Scale Revised (CESD-R) scale. Patient has to answer following questions: “How often in the past week did you feel like everything you did was an effort? How often in the past week did you feel like you could not get going?” The possible answers are: often (≥3 days) or not often, when the feeling is present in 0 to 2 days. Positive answer is when the patient says “often.”The last criterion is weight loss weight exceeding 10 pounds (appr. 4.5 kg) unintentionally in the past year.

Patients in whom 1 or 2 criteria are present will be assigned as pre-frail.

The Lawton IADL score is incorporated into CSHA Clinical Frailty Scale for description of mild to severe degrees of frailty.^[14]^ Moreover, even a single deficit in IADL score increases mortality rate by 56% in a cohort of patients with heart failure.^[15]^ We will compare patients with no deficits (IADL score equal to 24 points) with patients with different degrees of impairment (IADL score no >23 points).

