## Expected results and possible pitfalls

3

We expect to obtain results which will be evaluable in 3 categories: cross-sectional, baseline demographics, short-term longitudinal results of interventional treatment, and long-term follow-up results on adverse cardiovascular outcomes. We hope that we will be able to distinguish several clinical groups of patients, according to frailty status and relevant to procedural risk, like low-risk, medium-risk, and high-risk, or relevant to patient's clinical benefit. The major possible pitfalls of the study, that we must be aware of, are as follows. Our study is a single center, thus the extension of our results to community dwelling population or patients of other races will require discussion. Second, we are recruiting coronary artery disease patients only, but substantial proportion of them will have concomitant heart failure. Heart failure associated diminished functional capacity may mimic or be a true component of frailty. Heart failure in frail elderly patients may be considered as inseparable triangle.^[27]^ At the same time, active angina may also limit patients’ gait speed and result in over-diagnosing of frailty. In the population of truly pre-frail patients, stressors such as disease exacerbations, or hospital admission may result in dynamic transition to frail status. Thus, we must be aware of primary and secondary frailty, and its dynamic nature.^[27,28]^ We have diligently applied Fried frailty score as the most evaluator-independent and reproducible tool to assess frailty and compare its distribution with other populations.

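### The low-activity criterion of the Fried score pairs a 12-year recall window with weekly calorie cut-offs, which does not fit a score of current frailty

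*Protocol article*

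**What the plan says.** Section 2.2 of the protocol article (Frailty assessment with Fried frailty scale and IADL score) defines frailty by a count: "We recognize frailty if ≥3 out of 5 following criteria are met". The class below it is also fixed there: "Patients in whom 1 or 2 criteria are present will be assigned as pre-frail".

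For the activity criterion the article names the instrument ("Low physical activity is assessed by Minnesota Leisure Time Activity questionnaire") and the threshold: "The result is positive when calorie expenditure per week is lower than 270 kcal/wk in women and <383 kcal/wk in men". It mentions an in-house Excel template for the calculation. It then gives the period covered: "We are assessing the physical activity from the recent 12 years". It does not say how activity over that period becomes a weekly figure.

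The other criteria refer to the present or the recent past. Gait speed and grip strength are tested on the patient. Exhaustion is asked about as "How often in the past week did you feel like everything you did was an effort", with a second question over the same week. Weight loss counts if it occurred "unintentionally in the past year".

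**The concern.** A threshold in kcal per week describes how active a person is now. A 12-year window describes a long stretch of past life. The two do not belong together in a score that the Introduction says is reported before discharge and used as a predictor. Section 3 (Expected results and possible pitfalls) itself stresses that frailty is dynamic and that a patient can become frail through illness or admission. An activity history of 12 years could hardly register such a change.

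The Fried class is one of the study's two main exposures. Under section 2.8 it also defines the groups across which the risk scores are compared, and under the Discussion its predictive value is compared with that of IADL. In section 3 the authors justify it as the "most evaluator-independent and reproducible tool to assess frailty and compare its distribution with other populations". An activity criterion with a different window from the one its cut-offs were made for would weaken that comparison.

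**Working it through.** **1. Time frames of the five criteria (section 2.2).**

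| Criterion | Time frame |
|---|---|
| Slowness | measured at assessment |
| Weakness | measured at assessment |
| Exhaustion | past week |
| Weight loss | past year |
| Low activity | 12 years, against a kcal/wk cut-off |

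The activity window is 12 times the longest of the others. No other section of the article corrects or explains it. The plan gives no figure on this point to reproduce.

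**2. What the stated window would do, if averaged.** *Assumption, not in the article:* weekly expenditure is the plain mean over 12 years. For a patient at 0 kcal/wk for the last *y* years and at a constant level *L* before that,

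mean = *L* × (12 − *y*)/12,

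so the patient reaches cut-off *c*, and scores as active, when *L* ≥ *c* × 12/(12 − *y*).

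| Inactive for the last | Men, *c* = 383 | Women, *c* = 270 |
|---|---|---|
| 1 year | 383 × 12/11 = 417.8 | 270 × 12/11 = 294.5 |
| 2 years | 383 × 12/10 = 459.6 | 270 × 12/10 = 324.0 |
| 3 years | 383 × 12/9 = 510.7 | 270 × 12/9 = 360.0 |
| 5 years | 383 × 12/7 = 656.6 | 270 × 12/7 = 462.9 |

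If activity instead falls in a straight line to zero, the mean is half the starting level. The patient scores as active if the start was at least 2 × 383 = 766 (men) or 2 × 270 = 540 (women) kcal/wk.

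So an earlier level only a little above the cut-off is enough for a man or woman who has done nothing for a year to be scored as active. A patient who was below the cut-off throughout still scores positive.

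**3. Who changes class.** Let *k* be the number of the other four criteria that are met. Missing the activity point has these effects:

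- *k* = 0: count goes from 1 to 0, pre-frail to non-frail.
- *k* = 1: count goes from 2 to 1, still pre-frail.
- *k* = 2: count goes from 3 to 2, frail to pre-frail.
- *k* = 3 or 4: count stays at 3 or more, still frail.

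Only *k* = 0 and *k* = 2 matter.

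**4. Illustration of size.** *Assumptions, not in the article:* five independent criteria, each with 30% prevalence.

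- P(*k* = 2) = 6 × 0.3² × 0.7² = 0.2646.
- P(*k* ≥ 3) = 4 × 0.3³ × 0.7 + 0.3⁴ = 0.0837.
- Frailty with a share *m* of true low-activity cases missed = 0.0837 + 0.2646 × 0.3 × (1 − *m*).

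| *m* | Frail |
|---|---|
| 0 | 16.3% |
| 25% | 14.3% |
| 50% | 12.3% |
| 100% | 8.4% |

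This shows how the 3-of-5 rule passes the error on. It does not estimate the error in this study, because neither *m* nor the prevalences and correlations of the criteria are given.

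**The case against.** The strongest reply is that the 12 years is a misprint. It is one sentence, in a list whose other periods are a week and a year, and scoring is done by a template that may use a sensible period. In that case no patient is misclassified. The document cannot settle this, so the reply stands against any claim of demonstrated bias. It does not rescue the text: the sentence is a stated operating rule for a main exposure, and anyone who follows it would score differently from the study.

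The article also states no averaging rule, so the arithmetic above is conditional even if the window is real.

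A reader might infer more: that frailty is under-diagnosed in FRAPICA, that the template is wrong, or that comparison with other populations is invalid. The article does not support these readings. Nothing shows what the template uses. Most combinations of criteria keep their class when the activity point is lost. Section 3 notes that angina may slow gait and lead to over-diagnosis, so the net direction of error in the score is not established either. Nor does the window always reach back to middle age: eligibility starts at 65 with no stated upper limit, and for an 80-year-old it covers ages 68 to 80. IADL, the other main predictor, is untouched.

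**Conclusion.** The definition is wrong as written and should be corrected: a 12-year window is incompatible with a weekly cut-off in a score of current state.

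The consequence is conditional. If 12 years was used and averaged, patients whose activity fell recently can score as active; after one inactive year, an earlier level of about 418 kcal/wk (men) or 295 kcal/wk (women) suffices. Some patients with exactly three criteria including low activity would then drop from frail to pre-frail, and some with low activity alone from pre-frail to non-frail. How many cannot be derived from the document. If the figure is a misprint, there is no bias and only the text is at fault.

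**What to change.** - Replace the 12 years in section 2.2 with the recent recall window for which the cited scale's 270 and 383 kcal/wk cut-offs were defined. The authors must take that window from their source; the article does not give it.
- State how activity over that window is converted to kcal per week.
- Verify that the Excel template uses the same window and conversion.
- Re-score patients already assessed only if a 12-year window was actually used.

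The cost is a one-line correction, one sentence on the conversion and a check of the template. Re-scoring adds work only in the last case, and would need activity entries detailed enough to recover the shorter window. Whether the template holds them is not stated.
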